#### Contextual factors

Comparisons between urban and rural communities will be conducted by linear mixed models for continuous variables (ie BMI) and generalized linear mixed model (GLMM) l for categorical variables (ie CVD events), in each case treating community as the random effect. Using a similar model, unadjusted correlations will be estimated between the perceived (EPOCH-2) and objective environmental measures (EPOCH-1) with the continuous or categorical outcomes. Multilevel modeling will be used to evaluate the relation between exposures at the community (FSA-level) and individual level with outcomes for each individual. All models will examine both perceived and objective environmental measures as covariates adjusted for individual and community socio-demographics. Interaction terms between urban and rural and the perceived and objective environmental measures will be investigated to determine if the contextual factors differ based on the type of community ie urban or rural. The contribution of variance in outcomes explained by community risk factors as opposed to the individual risk factors will be quantified using the variance partition coefficient from each model. For the continuous outcomes, linear multi-level modeling will be used. For categorical outcomes (ie CVD), similar generalized linear multi-level models will be fit. Models will be adjusted a priori for individual (age, sex, ethnicity, and household income) and community variables.

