## The specific objectives of the CAHHM are

To understand the role of socio-environmental and contextual factors (such as societal structure, activity, nutrition, social and tobacco environments, and access to health services) on CV risk factors, subclinical disease, and clinical CV events at the individual and population levels. This includes the impact of contextual factors on geographic variation in CVD (ie rural vs. urban, and east to west gradient), and their relative impact compared to individual level factors.To characterize the unique patterns of contextual factors as well as acculturation, cultural continuity, and migration experience as related to individual CV risk factors, health service utilization (ie screening, access to diagnostics and treatments), and clinical outcomes among high risk ethnic groups including South Asian, Chinese, and African origin, as well as reserve-based First Nations people from across Canada.To identify early subclinical dysfunction and tissue abnormalities in the brain, blood vessels and the heart, to characterize abdominal and pericardial fat distribution, and to investigate the association of dysfunction with contextual and individual determinants. Furthermore, the data will shed light on the predictive value of novel markers of subclinical abnormalities and dysfunction on the development of clinical events related to cardiac, vascular and cognitive dysfunction.

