#### Analysis

To investigate the association between risk factors and subclinical MRI findings linear (visceral fat) and logistic (RWMA, covert stroke, liver fat %) regression models must be built separately for each MRI outcome used as the dependent variable. Exposures such as age, sex, ethnicity, history of hypertension, diabetes, waist circumference, apolipoprotein B/A ratio, current smoking, physical activity, selected dietary (ie prudent diet score, or ratio polyunsaturated fat/saturated fat), and measures of cognitive function (ie when covert stroke is the outcome) will first be tested univariately, and exposures with a *P* < 0.10 will be taken forward and tested in multivariate regression models. If ethnicity is found to be an independent predictor of an MRI outcome, it will be tested with a composite CV risk score for an interaction with the outcome.

After 5 years, when enough CVD events have been accrued and ascertained through record linkage, the MRI subclinical exposure of covert stroke, global or regional ventricular function abnormalities, liver fat and visceral fat will be tested versus CVD and death to determine their predictive value of clinical events using the area under the curve (C statistics), and net reclassification improvement methods [68].

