### Anticipated challenges

The CAHHM initiative is a massive undertaking to coordinate the recruitment of new and existing cohort participants from 7 existing cohorts and a new First Nations cohort, facilitating MRI scanning in urban, rural and remote regions, and conducting record linkage for clinical events using Health Card Number, across provinces, at multiple future time points. However, the study is robustly underway due to the strong commitment of interested participants, researchers, academic institutions, and funding agencies.

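### The variance partition coefficient from adjusted models does not measure variance explained by community versus individual factors, so the comparison of their impact in the first objective can point the wrong way

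*Protocol article*

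**What the plan says.** The first specific objective covers the role of contextual factors in CV risk factors, subclinical disease and clinical CV events. It also asks for "their relative impact compared to individual level factors".

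The Contextual factors section (under Statistical considerations) supplies the method. Multilevel models relate FSA-level and individual-level exposures to each person's outcome. All of them carry the perceived and objective environment measures as covariates, with adjustment for individual and community variables. For the relative-impact question, the section names "The contribution of variance in outcomes explained by community risk factors as opposed to the individual risk factors" and says that it "will be quantified using the variance partition coefficient from each model". No null model and no nested sequence of models is described.

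For events, the same section compares urban and rural communities with a "generalized linear mixed model (GLMM) l for categorical variables (ie CVD events", taking community as the random effect. It later adds: "For categorical outcomes (ie CVD), similar generalized linear multi-level models will be fit". It mentions no time scale, offset or censoring. Under Anticipated challenges, record linkage is described as running "across provinces, at multiple future time points".

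**The concern.** A VPC is the between-cluster variance divided by the sum of the between-cluster and within-cluster variances that the model leaves over. Once covariates are in the model, both terms are residual. The coefficient then says how much of what remains unexplained is shared by people in the same FSA. It does not say how much the measured community factors explain. Because there is only one coefficient per model, there is no counterpart for the individual factors to set beside it.

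If it is read as the sentence invites, strong community factors shrink the figure that is meant to show their importance. Strong individual factors inflate it. The study intends its results to inform policy on communities, so a reversed ranking of contextual and individual influences would matter.

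The secondary worry is that CVD events are classed as categorical. If people in some communities are followed for longer than others, a yes/no model reads the extra time as extra risk.

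**Working it through.** **Plan's own figures.** The article gives no number for the contextual models. The nearest figure on CVD events is in Table 7: N 7000, incidence 0.0598, prevalence of regional wall motion abnormality 0.253, hazard ratio 2.60, power above 0.99. Schoenfeld's formula with 7000 × 0.0598 = 418.6 events and two-sided alpha 0.05 (assumed) also gives power above 0.99. That figure is not in dispute.

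**VPC, continuous outcome.** The inputs are assumed, since the article states no variance components: FSA variance 5, individual variance 95, total 100. For simplicity, community factors act only on the FSA variance and individual factors only on the individual variance. VPC = residual FSA variance / (residual FSA variance + residual individual variance).

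| Model | Residual FSA | Residual individual | VPC | Total variance explained by community factors | By individual factors |
|---|---|---|---|---|---|
| Null | 5 | 95 | 5/100 = 5.0% | 0% | 0% |
| Community factors remove 60% of FSA variance | 2 | 95 | 2/97 = 2.1% | 3% | 0% |
| Individual factors remove 20 units | 5 | 75 | 5/80 = 6.3% | 0% | 20% |
| Both | 2 | 75 | 2/77 = 2.6% | 3% | 20% |

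In the last row neither the 3% nor the 20% can be recovered from the 2.6%.

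**Range.** Keep the 5/95 split and let community factors explain 0%, 50%, 90% or 100% of the FSA variance. Their share of the total is 0%, 2.5%, 4.5% or 5.0%, while the VPC is 5.0%, 2.6%, 0.5% or 0.0%. The two move in opposite directions throughout. If individual factors explain 30% of the individual variance and community factors explain nothing, the VPC rises to 5/(5 + 66.5) = 7.0%.

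**VPC, binary outcome.** The value depends on a scale that the section does not name. With an assumed random-intercept variance of 0.1, the latent logistic VPC is 0.1/(0.1 + π²/3) = 0.1/3.39, about 3%. On the response scale at 5.98% risk it is about 0.6% (by simulation). On the latent scale the individual-level variance is fixed at π²/3, so adding covariates rescales the other terms and VPCs are not directly comparable between models.

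**Follow-up time (conditional).** The 5-year risk of 5.98% is from the power section; the follow-up differences are assumed. With a constant hazard λ = −ln(1 − 0.0598)/5, risk at t years is 1 − exp(−λt). For a true hazard ratio of 1.0:

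| Follow-up compared | Risks | Spurious odds ratio |
|---|---|---|
| 5 vs 5 years | 5.98% vs 5.98% | 1.00 |
| 5 vs 4.5 years | 5.98% vs 5.40% | 1.115 |
| 5 vs 4 years | 5.98% vs 4.81% | 1.258 |
| 5 vs 3 years | 5.98% vs 3.63% | 1.688 |

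With equal follow-up the change of scale is slight: hazard ratios of 1.2, 1.5, 2.0 and 2.6 become odds ratios of 1.21, 1.52, 2.06 and 2.73.

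**The case against.** On the VPC, the phrase about each model could mean that VPCs will be compared across models, and the variance components behind a VPC are those needed for a proportional change in variance. The coefficient misleads only if an adjusted value is read as an effect size. That is fair as far as it goes. But the section describes no null or nested models, says that all models carry the environmental covariates, and names the VPC itself as the measure of variance explained. This is a stated method, not a detail left to a fuller plan.

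The usual remedy has limits too. In logistic models the change in FSA variance is itself affected by rescaling. A frailty model for event times has no ordinary individual-level residual variance. Correlated blocks of predictors have no unique split of R². These points stand and shape the fix.

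Three stronger readings are tempting, and the documents do not support them:

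- A reader might infer that the whole first objective is answered with the wrong quantities. It also covers risk factors and subclinical disease, and for associations with those outcomes mixed models with a community random effect are suitable.
- A reader might infer that geographic contrasts in CVD are confounded with follow-up time. The word categorical suggests a yes/no model, but no link or offset is excluded, and a Poisson model with a person-time offset is itself a GLMM. The article gives no follow-up by community. Passive linkage, with 99.2% of the first 1000 participants consenting to provide a health card number, makes heavy loss less likely. Staggered entry and linkage dates remain possible.
- A reader might fault the Analysis section for assessing MRI markers "using the area under the curve (C statistics), and net reclassification improvement methods" when power is stated for hazard ratios. Both measures can be computed from a Cox model. The underlying model is unstated in a condensed article, not wrongly stated.

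**Conclusion.** The point holds for the relative-impact part of the first objective. The article fixes a statistic that does not measure what the sentence says it measures. In the illustration, community factors worth 3% of total variance lower the VPC from 5.0% to 2.1%, and individual factors raise it to 6.3% without any change in community effects. The direction follows from the definition; the sizes rest on the assumed 5/95 split and on each block acting at one level only.

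The follow-up point is secondary and conditional. It has no effect if follow-up is equal across communities, and its size otherwise (odds ratio 1.115 to 1.688 for a gap of half a year to two years) rests on gaps that the documents do not report.

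**What to change.** Replace the VPC sentence with a nested sequence: null, individual factors only, community factors only, and both. Report the proportional change in between-FSA variance and in individual-level variance from the null model. For continuous outcomes add an R² partitioned between the two blocks, with any share common to both shown separately. Keep the VPC only to describe clustering. For binary outcomes, state the scale and allow for rescaling across the nested models.

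For incident CVD, state how follow-up time enters. If it can differ by community, use for example a Poisson GLMM with a log person-time offset, or a Cox model with a shared FSA frailty, censored at each province's last linkage date. The R² partition should not be carried over to the frailty model.

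The cost is plan wording, a little more analysis and a summary less compact than one coefficient. The design does not change.

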### Contextual factors measured at the individual and community level

Data describing contextual factors that characterize the nutrition, physical and tobacco environments of communities from which participants are recruited as well as individual behaviors in these domains are collected using the modified EPOCH-1 and modified EPOCH-2 questionnaires modified from the PURE study [57, 58]. EPOCH-1 is a standardized community audit developed and validated in the PURE study [57] and EPOCH-2 captures individual’s perceptions of their food, activity, and tobacco environment also developed in the PURE study [58] with added questions on social ties, alcohol use, and workplace activity and food choices and behaviors.

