### Community audits

To study community level contextual factors as related to individual risk factors and clinical events we retrospectively defined “community” as participants are already recruited. After review of the communities from which participants in the 5 CPTP cohorts and the 2 partner cohorts originate, the forward sortation areas (FSA) was deemed to be the optimal community unit. (Table 5) We have chosen the FSA as our definition of community because: 1) there was low representation of cohort participants from census tracts in rural areas and eastern provinces of Canada, 2) the FSA are those reported by census respondents for their place of residence and this information collected from the census is available in aggregate for each FSA. This census information includes age, sex, marital status, families and household information, housing costs, mobility and migration, immigration and citizenship, income and earnings, and ethnic groups. This is balanced by some limitations of this approach include: for certain highly populated urban areas the FSA is too large to well represent the community—in this scenario, we surveyed multiple postal codes within the FSA to capture the diversity. The community level information will be used together with self-reported perception of community environment as well as behavior patterns, ie shopping, activity, and workplace. These will be used together with objective measures of the built environment from publically available databases (ie streetsmart walk-score at www.walkscore.com), which provides information by postal code on neighborhood walkability, land use mix, transportation availability and location of food retail outlets [59].

**Table 5 Tab5:** Number of FSAs represented by the 7 Cohorts making up the CAHHM

Province	FSA total	FSA to be assessed in CAHHM (Postal Codes)*	# in reliability assessment (%)	Number of postal codes within FSAs being assessed (sum)
BC	190	190 (+50)		112904
AB	153	153 (+46)	40 (21.1 %)	76924
SK	49	49 (+8)		21541
MN	66	66 (+12)		23943
ON	526	526 (+208)		282123
QC	419	419 (+108)	55 (10.4 %)	215565
Atlantic	230	230 (+72)		92809
NS	77	77 (+26)		28171
NB	111	111 (+30)		59530
PEI	7	7 (+2)		3995
N/L	35	35 (+14)		1113

*For FSA with income discrepancies across postal codes within the FSA, 2 audits were done to reflect the 25^th^ percentile an

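### The adjusted contextual models all pair the audited environment with the participant's perception of it, so no adjusted estimate of the environment's total effect is planned

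*Protocol article*

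**What the plan says.** The rule is in the Protocol article, Statistical considerations, Contextual factors: "All models will examine both perceived and objective environmental measures as covariates adjusted for individual and community socio-demographics". The same section adds: "Models will be adjusted a priori for individual (age, sex, ethnicity, and household income) and community variables". EPOCH-2 is not in that list of adjusters. The one separate look at each measure comes earlier in the section, where "unadjusted correlations will be estimated between the perceived (EPOCH-2) and objective environmental measures (EPOCH-1") and the continuous or categorical outcomes. Urban-rural comparisons by mixed model are also planned.

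The two instruments are defined under Contextual factors measured at the individual and community level. Of the objective measure it says: "EPOCH-1 is a standardized community audit developed and validated in the PURE study". EPOCH-2 records individuals' "perceptions of their food, activity, and tobacco environment", "with added questions on social ties, alcohol use, and workplace activity and food choices and behaviors". The Community audits section points the same way on combining them: "The community level information will be used together with self-reported perception of community environment".

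Objective 1 concerns the role of contextual factors in risk factors, subclinical disease and events. It continues: "This includes the impact of contextual factors on geographic variation in CVD". The same sentence then asks for their impact relative to individual-level factors. The Discussion speaks of the influence of context on risk factors and expects the results to inform policy.

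**The concern.** EPOCH-1 records what is in the community. EPOCH-2 records what the participant believes is there, in the same food, activity and tobacco domains, and adds some behaviour items. Perception is plausibly in part a consequence of the real environment, and behaviour may be too. Adjusting for a consequence of the exposure removes the part of the effect that passes through it. What is left is a direct effect.

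Policy can change the environment itself, so the quantity needed is what happens to outcomes when the environment differs, by whatever route. The plan names no adjusted model that gives this. It declares no direct-effect estimand and no mediation analysis under which the joint coefficient would be the intended target.

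There is a second risk. EPOCH-2 is a self-report listed among the baseline measures (Table 2). If a participant's health or habits influence both perception and the outcome, conditioning on perception opens a non-causal path between the audited environment and the outcome. The joint coefficient would then not be a clean direct effect either.

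**Working it through.** The article gives no effect size, power or sample-size figure for the contextual models, so there is no stated figure to reproduce. Every path value below is an assumption.

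**Set-up.** Standardised linear paths:
- a: audited environment to perception
- b: perception to outcome
- c: audited environment directly to outcome

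The model with EPOCH-1 and confounders estimates the total effect, c + ab. The joint model estimates c. The share removed is ab/(c + ab).

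**Same-sign paths.**

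| b | c | a = 0.3 | a = 0.5 | a = 0.7 |
|---|---|---|---|---|
| 0.05 | 0.15 | 0.015/0.165 = 9% | 0.025/0.175 = 14% | 0.035/0.185 = 19% |
| 0.10 | 0.10 | 0.03/0.13 = 23% | 0.05/0.15 = 33% | 0.07/0.17 = 41% |
| 0.15 | 0.05 | 0.045/0.095 = 47% | 0.075/0.125 = 60% | 0.105/0.155 = 68% |

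**Opposite-sign paths.** With c = 0.10, a = 0.5 and b = -0.10, the total is 0.10 - 0.05 = 0.05. The joint model reports 0.10, twice the total. The direction of the discrepancy is therefore not fixed.

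**Check in a multilevel model.** Random-intercept linear models were fitted to simulated data: 7000 participants (the planned sample), an assumed 700 communities of 10, and five replicates per setting. Settings were c = 0.10, a = 0.2, 0.4 or 0.6, and b = 0.1 or 0.2.
- The true total runs from 0.10 + 0.02 = 0.12 to 0.10 + 0.12 = 0.22. The expected loss runs from 0.02/0.12 = 17% to 0.12/0.22 = 55%.
- Without perception, the fitted EPOCH-1 coefficient was 0.122 to 0.210, near the total in each setting.
- With perception, it was 0.089 to 0.102, near c.

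**Shared unmeasured cause.** Let an unmeasured variable affect both perception and outcome with coefficient u = 0.3.
- With perception scaled to variance 1, the joint coefficient is c - a·u²/(1 - a²). This gives 0.10 - 0.018/0.96 = 0.081 at a = 0.2, 0.10 - 0.036/0.84 = 0.057 at a = 0.4, and 0.10 - 0.054/0.64 = 0.016 at a = 0.6.
- The simulation gave 0.025 to 0.085, which is 32% to 89% below the total. Five replicates leave visible noise.
- The model without perception stayed at 0.120 to 0.226.

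**Precision.** A single-level variance inflation of 1/(1 - a²) gives 1.10 at a = 0.3 and 1.96 at a = 0.7. The plan uses community random effects with EPOCH-1 at community level. There, with 10 to 20 participants per community and residual intraclass correlation 0.02 to 0.10 (both assumed), the inflation is 1.03 to 1.08 at a = 0.3 and 1.31 to 1.81 at a = 0.7. This is a minor part of the point.

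**The case against.** **Joint modelling serves part of Objective 1.** That objective also asks how contextual factors compare with individual-level factors, and a model holding both measures speaks to this. This stands: the joint model should be kept, and a direct effect is a different estimand and not in itself an error. It does not supply the total effect that the rest of the objective asks for.

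**EPOCH-2 is itself an exposure.** The article presents it beside EPOCH-1 as a contextual measure and leaves it out of the a priori adjusters, so the sentence could mean that each measure is examined in turn. That reading is possible but strained, since the sentence covers all models and calls both measures covariates. If it is the intended meaning, the sentence needs rewording.

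**A condensed article leaves the order of models to a fuller plan.** That would answer a silence. Here the article states a rule for all models.

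**Mediation is not documented.** This stands. The article also concedes that the forward sortation area can be too large to represent dense urban communities, so perception may capture local conditions that the audit misses. An estimate from EPOCH-1 alone is then the effect of the environment as audited, with its measurement error.

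**Stronger readings to avoid.** A reader might infer that every contextual analysis contains both measures. The unadjusted correlations and the urban-rural comparisons show otherwise. A reader might also infer that the environment's effect is necessarily understated and that policy conclusions would be wrong. The opposite-sign example shows that the direction is open, and no path value comes from the documents.

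**Conclusion.** The point holds for the adjusted multilevel models. As written, they all condition the audited environment on the participant's perception of it, and the only separate look at each measure carries no confounder adjustment. No adjusted estimate of the environment's total effect is therefore planned.

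The consequence depends on perception being partly caused by the real environment. That is natural given what the two instruments ask, but it is an assumption. Under it, the EPOCH-1 coefficient is at best an effect net of perception. The 9% to 68% range illustrates assumed same-sign paths and is not an estimate for this cohort. The discrepancy could be larger if perception and outcome share unmeasured causes, or reversed if the paths have opposite signs. The documents support the conclusion that the reported effect could mislead about the environment; they do not establish by how much or in which direction.

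**What to change.** For each outcome, prespecify three adjusted analyses:

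1. **Main estimate of the environment's total effect:** EPOCH-1 with the a priori individual and community socio-demographic confounders, without EPOCH-2.
2. **Perception:** EPOCH-2 in its own model with the same confounders.
3. **Secondary joint model:** both measures, for their relative contribution, with the EPOCH-1 coefficient labelled as the effect net of perception.

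Reword the sentence that now places both measures in all models. If the intention was to examine each in turn, the same rewording settles it.

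The cost is a change of analysis wording and one or two extra models per outcome. No new data are needed. Naming the main model before analysis also avoids choosing between the versions once results are known.
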